### Sample size calculation

To replace colonoscopy—the current gold standard for diagnosing bowel conditions—and/or CTC, FIT and VOC analysis requires a very high sensitivity to avoid false negatives. High specificity is also desirable, to reduce false positives. Based on our previous study, the sensitivity of FIT and VOC analysis to detect CRC was 97%, comparable to colonoscopy. Therefore, the sample size was determined to achieve a sensitivity of at least 97% with a 95% CI width of 5% (Zhou-Li method^19^ as described in box 1). The required number of participants with SBD to achieve this sensitivity is 200. Figure 2 shows CIs for different observed sensitivity cases of SBD (150, 200, 250). Figure 3 shows the widths of the CI limits are narrower and wider when the observed sensitivity is above or below 97%,^13^ respectively. This sample size is also robust to negative predictive value (NPV), an outcome that is of interest as a high NPV suggests that participants without SBD would avoid having colonoscopy examination. Assuming the prevalence of SBD in the study population is 19%, then 1053 participants are required. Based on our previous study,^13^ the return rate of both stool and urine samples that are eligible for analysis is about 55% resulting in a total required sample size of 1915 participants across multiple UK sites within a 24-month period.

Box 1Sample size determination based on CI methodThe Zhou Li CI is 
$\left(\frac{e^{LL}}{1+e^{LL}},\frac{e^{UL}}{1+e^{UL}}\right)\left(\frac{e^{LL}}{1+e^{LL}},\frac{e^{UL}}{1+e^{UL}}\right)$
 where 
$LL=ln\left(\frac{\bar{S}\bar{e}}{1-\hat{Se}}\right)-\frac{1}{\sqrt{n\hat{Se}(1-\hat{Se})}}g^{-1}(z_{1-\alpha /2})$
, 
$UL=ln\left(\frac{\bar{S}\bar{e}}{1-\hat{Se}}\right)-\frac{1}{\sqrt{n\hat{Se}(1-\hat{Se})}}g^{-1}(z_{\alpha /2})$
, 
$g^{-1}(x)=-\sqrt{n}\left(\frac{6}{\hat{\gamma }}\right)\left\{{\left[1-\frac{\hat{\gamma }}{2}\left(\frac{x}{\sqrt{n}}-\frac{\hat{\gamma }}{6n}\right)\right]}^{1/3}-1\right\}$
and
$\hat{\gamma }=\frac{1-2\bar{S\bar{e}}}{\hat{Se}(1-\hat{Se})}$

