### Secondary outcome analyses

Secondary outcomes include: ROC of FIT plus VOC to develop an optimum thresholds for SBD detection; sensitivity, specificity, PPV and NPV estimates and their corresponding 95% CI for each individual condition of SBD (CRC, colorectal adenomas and IBD) by each individual test and combination rules; compliance rates (return of samples); the types of SBD and microscopic colitis, and the number of cases missed by CTC, FIT and VOC analyses; potential number of avoidable colonoscopies and CTCs in patients without SBD; total NHS and personal social services costs and total quality of adjusted life years (QALY) associated with each option. To find the optimal thresholds of FIT and VOC we will first plot the ROC curves of both tests individually to find the individual optimal thresholds (the one that gives the greatest specificity while achieving 97% sensitivity). Second, we will plot combinations of the two tests in the ROC space and similarly, choose the combination of thresholds which has greatest specificity while achieving the required 97% sensitivity to avoid colonoscopy. The combined thresholds of FIT and VOC in the ROC space are calculated by combining every unit of FIT (from 10 to 120µgHb/g faeces) with every unit of the predicted probability of VOC (from 0.63 to 1). Both the ‘or’ and ‘and’ rules will be explored when combining the FIT and VOC results to define a case as either SBD positive or SBD negative. If both tests are in discordant then the diagnosis is negative. For each of the thresholds that we derive from the ROC curves, we will also report the NPV estimates. This will produce an overestimate of test accuracy, which we will use as a sensitivity analysis in the economic model, as a more optimistic assumption to demonstrate the range of uncertainty.

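### The secondary threshold search reports accuracy from the cases used to choose the thresholds; the admitted optimism, about 1 to 2 points of sensitivity for a pair, is neither estimated nor corrected

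*Protocol article*

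**What the plan says.** Under Secondary outcome analyses, the protocol article first finds an optimal cut-off for each test alone, then combines FIT cut-offs from 10 to 120 µgHb/g with VOC predicted probabilities from 0.63 to 1. The rule for the pair is to "choose the combination of thresholds which has greatest specificity while achieving the required 97% sensitivity to avoid colonoscopy". NPV is also reported for each threshold derived this way. The section then states: "This will produce an overestimate of test accuracy, which we will use as a sensitivity analysis in the economic model". It labels that scenario as optimistic and gives its purpose as showing how wide the uncertainty is. No internal validation or optimism correction is named.

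The number of cases comes from Sample size calculation: "The required number of participants with SBD to achieve this sensitivity is 200". It continues: "Assuming the prevalence of SBD in the study population is 19%, then 1053 participants are required".

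Two other statements limit the reach of the point. The Abstract says the diagnostic thresholds are set in advance and that testing others is exploratory. Primary outcome analysis fixes the primary rule (FIT above 10 or VOC above 0.63) and sends those estimates to the economic model.

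**The concern.** A cut-off chosen because it just meets an observed 97% tends to be one whose misses happened to be few in this sample. In new patients it will, on average, miss more. A pair chosen from a large grid has more room to exploit chance than a single cut-off, so its bias is larger.

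The plan recognises the direction of the bias but treats it as a reason to call the figure optimistic. Selection bias is not parameter uncertainty, and the same data can estimate its size. What is at stake is the credibility of a listed secondary outcome, the optimum thresholds for SBD, and of one economic scenario. Sample size calculation says the dual test needs very high sensitivity to avoid false negatives. Against that aim, a true sensitivity of 95.5% in place of 97% means 45 rather than 30 missed per 1,000 cases.

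**Working it through.** **Inputs.** From the protocol article: 97% target, 200 cases, prevalence 19%, 1053 analysable participants (so 1053 − 200 = 853 without SBD), 55% return rate, and the search grid. Assumed: a VOC step of 0.01 and the score distributions, which the document does not give.

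**The plan's own figures reproduce.** The Zhou-Li interval at sensitivity 0.97 and n = 200 runs from 0.9387 to 0.9877, a width of 0.049 against the planned 5%. Then 200/0.19 = 1052.6, rounded up to 1053, and 1053/0.55 = 1914.5, rounded up to 1915.

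**One threshold (distribution-free for continuous scores).** An observed 97% in 200 cases allows 200 × 0.03 = 6 misses. The highest cut-off allowing 6 misses sits at the seventh smallest score among the cases. The true miss rate there follows Beta(7, 194).
- Expected true sensitivity = 1 − 7/201 = 96.5%.
- P(true sensitivity < 97%) = P(Bin(200, 0.03) ≤ 6) = 0.606.

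**A pair under the either-test-positive rule (simulation).** The grid has 111 FIT values × 38 VOC values = 4,218 pairs. Data were 200 cases and 853 non-cases with Gaussian log FIT (SD 1.8) and Gaussian logit VOC (SD 1.0). Seven scenarios had single-test sensitivity of 80% to 95%, specificity of 60% to 75%, and latent correlation of 0 or 0.3.
- Apparent sensitivity of the chosen pair: 97.0%.
- True sensitivity: 95.1% to 95.6%.
- P(true sensitivity < 97%): 0.83 to 0.97.
- Optimism in specificity: at most 0.5 points.

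A second simulation, with other Gaussian parameters and a coarser 40 × 38 grid, gave true sensitivity of 95.7% and 96.1% against apparent 97.0% and 96.9%. The probability of being below 97% was 0.83 in the first setting. In the second it was 0.66 or 0.84, depending on how searches that found no qualifying pair were counted. Together the runs put the optimism in sensitivity at about 1 to 2 points.

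**Structural check.** Both grid ranges start at the primary thresholds and only go up. Under the either-test-positive rule, no pair on the grid can have higher true sensitivity than the primary rule. If the primary rule were truly at exactly 97%, a qualifying pair would exist only when that rule itself shows at most 6 misses (probability 0.61), and no pair with a higher cut-off could then exceed 97%.

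**Does cross-validation recover the truth?** Ten-fold cross-validation of the whole search, three scenarios, up to 300 repeats each:

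| Single-test sensitivity | Apparent | True | Cross-validated | P(true < 97%) |
|---|---|---|---|---|
| 88% | 0.970 | 0.954 | 0.958 | 0.87 |
| 92% | 0.970 | 0.955 | 0.954 | 0.85 |
| 95% | 0.970 | 0.954 | 0.955 | 0.88 |

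The reported figure comes within about 0.4 points of the truth. The selected pair is the same, so the last column is not improved by the correction. Raising the selection target until the cross-validated value reached 97% moved true sensitivity to 96.1% to 96.6%, still below 97% in 57% to 73% of the repeats where this could be done, and cost about 3 to 5 points of specificity.

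**The case against.** The strongest reply is that the bias is disclosed and contained. The article says the figures are too high, uses them only as an optimistic economic scenario, calls the search exploratory, and rests its primary result on pre-set thresholds. The bias of 1 to 2 points is also smaller than the planned interval width of 5 points, and an analysis plan that is not shown may add internal validation. Most of this stands and sets the limits of the point. It does not remove it, because the article itself fixes the use of the uncorrected figure and gives no size for a bias that the same data can estimate.

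Four stronger readings are not supported.
- A reader might infer that the searched pair will be recommended for practice. The article says the study's results can inform national guidance, but does not tie that to the searched thresholds.
- A reader might infer that the main conclusions are compromised. They rest on the pre-set rule.
- A reader might call the economic scenario unattainable. It is declared as an optimistic bound, and the bias is modest.
- A reader might infer that cross-validation gives a pair meeting 97%. It corrects the estimate and leaves the pair as it is.

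It is also fair to say that the pair results depend on assumed distributions. Only the single-threshold result does not, and it is milder.

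**Conclusion.** The point holds for the secondary threshold search. Accuracy is reported from the cases used for selection, with an admitted but unquantified and uncorrected upward bias. For one threshold, true sensitivity averages 96.5% and falls below 97% with probability 0.61; this needs only 200 cases and continuous scores. For a pair under the either-test-positive rule, true sensitivity is about 95% to 96% on average, an optimism of about 1 to 2 points, and below 97% in most repeats; this rests on Gaussian latent scores and a VOC step of 0.01. The both-tests-positive rule, which the plan also explores, was not simulated. The primary accuracy results and main economic inputs are not affected. The change is worth making because a better estimate is available from the same participants.

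**What to change.** Run the whole selection, covering the individual cut-offs, the pair search and each combination rule, inside repeated 10-fold cross-validation or a bootstrap optimism correction. State in advance how a fold or resample with no qualifying pair is handled, since the structural check shows this can be common. Report the corrected sensitivity, specificity and NPV as the secondary result and use them in the economic threshold scenario. Label the uncorrected values as apparent performance and, if they are wanted in the model, keep them only as the optimistic bound.

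Do not describe the selected pair as achieving 97% unless its corrected estimate supports that. If the pair itself is meant to reach 97% with reasonable assurance, the selection rule must be stricter, or the pair must be tested on new data. For scale, allowing at most 2 misses in 200 for a single threshold brings P(true < 97%) down to P(Bin(200, 0.03) ≤ 2) = 0.059, at a cost in specificity.

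The correction needs no extra participants and little programming. Its cost is a reported sensitivity about 1 to 2 points less favourable.

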### Economic evaluation

An economic analysis will be carried out to determine the costs, benefits and overall cost-effectiveness of FIT +VOC versus FIT alone in selecting patients for colonoscopy or CTC among those with GI symptoms referred for investigation. The analysis will be carried out primarily from the perspective of NHS and it will employ a de novo analytic model built as part of this study. In line with recent literature,^7^ it is envisaged that the model will employ a multi-part structure, consisting of a decision tree to evaluate short-term cost and consequences accruing at the diagnosis stage followed by a state-transition model to capture the long-term (lifetime) outcomes associated with the diagnosed condition.

Calculations will consider key costs and consequences, including the costs and disutility associated with having a colonoscopy. Key model input will be drawn from the RECEDE study, including parameters related to the diagnostic characteristics of the compared options, estimates of the rate of adverse outcomes associated with colonoscopies (eg, bowel perforation and bleeding) and CTCs, as well as primary and secondary care resource use and preference-based health-related quality of life (utility) values associated with colonoscopy. The latter information will be needed to reflect the fact that undergoing a colonoscopy, including the bowel preparation and the procedure itself is an unpleasant activity which is likely to result in a temporary decrease in quality of life. Estimates of changes in quality of life will be obtained by administering a widely used and recommended generic questionnaire (EuroQol-5 Dimension-5 Level^21^) to a sample of 370 participants (20% of the total study sample) scheduled to undergo colonoscopy or CTC at (1) baseline (ie, when participant consent is received) (2) immediately prior to colonoscopy once the participant has fully completed bowel preparation, (3) 24 hours after the colonoscopy examination, (4) 72 hours post colonoscopy and (5) 3 weeks post colonoscopy. Use of resources, including NHS care, out of pocket payments and loss of income the participants may occur as a result of their colonoscopy will also be collected through patient questionnaires administered to the same sample of participants at 3 weeks post colonoscopy or CTC.

In line with recommendations, results will be presented in terms of total costs per additional QALY associated with FIT +VOC compared with FIT alone.^22^ Deterministic and probabilistic sensitivity analyses will be undertaken to explore the robustness of the obtained results to sample variability and plausible variations in key assumptions and employed analytical methods.^23 24^ The model will also form the basis for conducting value of information analysis, which will quantify the total expected cost due to the remaining uncertainty around the decision problem^25 26^

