**Methods and analysis:**

This is a multicentre, prospective diagnostic accuracy study evaluating whether stool FIT plus urine VOC compared with stool FIT alone improves detection of SBD in patients referred for colonoscopy or CTC due to persistent lower gastrointestinal symptoms. To ensure SBD is not missed, the dual test requires a high sensitivity, set at 97% with 95% CI width of 5%. Our assumption is that to achieve this sensitivity requires 200 participants with SBD. Further assuming 19% of all participants will have SBD and 55% of all participants will return both stool and urine samples we will recruit 1915 participants. The thresholds for FIT and VOC results diagnosing SBD have been pre-set. If either FIT or VOC exceeds the respective threshold, the participant will be classed as having suspected SBD. As an exploratory analysis we will be testing different thresholds. The reference comparator will be a complete colonoscopy or CTC. Secondary outcomes will look at optimising the FIT and VOC thresholds for SBD detection. An economic evaluation, using a denovo decision analytic model, will be carried out determine the costs, benefits and overall cost-effectiveness of FIT +VOC vs FIT followed by colonoscopy.

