## Introduction

There is currently a disparity between demand and available resources for colonoscopies and CT colonography (CTCs) within the National Health Service (NHS). Before the COVID-19 pandemic, around 300 000 patients were being referred annually to NHS trusts suspected of having colorectal cancer (CRC) and this number was rising.^1^ Most patients referred with suspected CRC are offered an invasive colonoscopy or CTC examination, but only 30% of these participants have significant bowel disease (SBD).^2^ SBD is defined as CRC, adenomatous polyps or inflammatory bowel disease (IBD).^3^ The remaining 70% have a normal examination with 30% of those having functional conditions such as irritable bowel syndrome (IBS).

Set against this there will remain a capacity shortfall for colonoscopies and CTCs for the foreseeable future. This limits capacity of the NHS to extend CRC detection within the Bowel Cancer Screening Programme (BCSP) or to investigate those who present through the emergency department. The imbalance between capacity and demand, coupled with a lack of an accurate triage test makes it difficult for the NHS to stratify patients who present with bowel symptoms to those most at risk of SBD. In the COVID-19 era, faecal immunochemical testing (FIT) is being introduced to triage patients who present with lower gastrointestinal (GI) symptoms.^4^ However, almost all patients still receive a colonoscopy or alternative colonic imaging at some time and the optimum threshold for FIT has yet to be determined. The National Institute for Health and Care Excellence (NICE) have recommended 10
μ
gHb/g faeces,^5^ whereas the BCSP have set a cut-off of 120
μ
gHb/g faeces.^6^ Even at the lower threshold some SBD cases can be missed.^2 7 8^ Previous data have shown that FIT alone (at a threshold of 7
μ
gHb/g faeces) has a sensitivity of 80%, 53% and 86% for CRC, adenomatous polyps and IBD respectively.^2^ A lower FIT threshold may reduce the number of false negatives but it will increase the number of unnecessary colonoscopies and CTCs in patients with no abnormalities (false positives). Moreover it will always miss cases of SBD where there is no bleeding, and a high proportion of malignant tumours never bleed.

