Thus, this study will test urine volatile organic compound (VOC) analysis alongside FIT to improve detection of SBD. VOCs are produced by metabolic responses to inflammation in the presence of illness, therefore they are disease specific.^9–11^ Previous work has identified key metabolites in inflammatory GI disease^12^ and, on its own, VOC analysis has a sensitivity of 80%, 92% and 86% for CRC, adenomatous polyps and IBD, respectively.^13 14^ When FIT and VOC are used in combination (FIT followed by VOC in the FIT negative), sensitivity of CRC improves from 80% to 97%, which is similar to the results of colonoscopy and CTC.^13 15^ Existing studies have already demonstrated the utility of VOC analysis in detecting IBD, coeliac disease and bile acid diarrhoea while also being negative in functional conditions such as IBS.^16 17^ Many patients with slightly raised FIT are found to have no SBD and we will examine the value of VOC in this group to see if a negative VOC can rule out SBD.

Therefore, the objective of this study is to investigate whether the combination of FIT and VOC analysis compared with FIT alone improves detection of SBD in patients who present with lower GI symptoms. This could be by both improving sensitivity in patients with FIT <10 and but also possibly by improving specificity in patients with slightly raised FIT but negative VOC. If correct, fewer patients will be referred for colonoscopies and CTCs, freeing up capacity and reducing NHS costs, while reducing disutility in patients who do not benefit from an invasive examination. Within the COVID-19 era, this has added importance. If the proposed method of dual testing proves effective then not only will hospital capacity be improved but also fewer patients will be required to undergo colonoscopies or CTCs; streamlining the patient pathway and reducing the risk of viral transmission if colonoscopy generates aerosols.

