### Primary outcome analysis

The primary outcome is diagnostic accuracy (sensitivity, specificity, NPV and positive predictive value (PPV)) of the dual index test FIT and VOC analysis. The ‘or’ rule will be utilised for the primary analysis whereby a FIT result of >10 µgHb/g faeces OR a VOC result with predicted probability >0.63 implies that the participant is suspected of having SBD and needs to be referred for colonoscopy or CTC. We will report 2×2 tables of test accuracy of the dual test by the reference standard (final report from the colonoscopy examination and confirmatory histology report of SBD which is either colon cancer, colorectal adenomas or IBD), alongside summary measures of sensitivity, specificity, NPV and PPV, and their 95% CIs. These test accuracy estimates will be used in the economic model.

We will analyse the combined FIT+VOC test results as both parallel (results from both tests are interpreted in combination) and serial testing (VOC analysis only performed if FIT is negative). The ‘or’ rule will be considered in the interpretation of both parallel and serial tests where the diagnosis is positive when either test is positive, and negative when both results are negative. In the serial test, if the FIT is positive, then the diagnosis is positive. If FIT is negative we will use the result from VOC analysis and if that is positive then the diagnosis is positive. Mathematically, both methods should give the same diagnostic results but will make a difference in the economic model.

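### In the base-case economic comparison with FIT alone, the OR rule can only add colonoscopies and CTCs at the selection stage; the reduction claimed in the Introduction needs an examine-all comparator that the model does not name

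*Protocol article*

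**What the plan says.** **Referral rule.** Under Primary outcome analysis, a "FIT result of >10 µgHb/g faeces OR a VOC result with predicted probability >0.63 implies that the participant is suspected of having SBD" and is to be referred. The serial version keeps the same logic: "In the serial test, if the FIT is positive, then the diagnosis is positive". Stool sample analysis uses the same FIT cut-off of 10. The accuracy estimates from this rule go into the economic model.

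**Economic comparison.** The Economic evaluation section sets the contrast as the "overall cost-effectiveness of FIT +VOC versus FIT alone in selecting patients for colonoscopy or CTC", and reports "total costs per additional QALY associated with FIT +VOC compared with FIT alone". The abstract words the comparator differently: "cost-effectiveness of FIT +VOC vs FIT followed by colonoscopy".

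**Expected effect.** The abstract gives better detection and fewer colonoscopies and CTCs as joint aims. The Introduction states the objective as FIT plus VOC compared with FIT alone and continues: "If correct, fewer patients will be referred for colonoscopies and CTCs, freeing up capacity and reducing NHS costs". It also describes current practice with FIT triage: "almost all patients still receive a colonoscopy or alternative colonic imaging at some time".

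**Count of procedures.** Secondary outcome analyses list the "potential number of avoidable colonoscopies and CTCs in patients without SBD" but do not say relative to which strategy. The same section explores higher thresholds and an AND rule. It takes the accuracy at the derived thresholds into the model only as a sensitivity analysis, which the authors themselves call optimistic.

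**The concern.** The study is motivated by freed endoscopy and imaging capacity and by disutility avoided in patients without significant bowel disease (SBD). The base-case economic contrast is set against a strategy relative to which the primary rule cannot reduce referrals. It will price extra procedures against extra cases found. That is a legitimate question, but it does not value the capacity that the Introduction says will be released. The value-of-information analysis, as described, rests on the same two options.

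The Introduction also moves directly from the comparison with FIT alone to the claim of fewer referrals. It hopes for better specificity in patients with slightly raised FIT and negative VOC, yet the primary rule refers every one of those patients. A reader of the results could see procedures rise in the economic section and fall in the avoidable-procedures count, with nothing in the plan to explain that the two use different reference strategies.

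**Working it through.** **1. The plan's own figures.** Sample size calculation: 200 SBD cases, prevalence 19%, return rate 55%. 200 / 0.19 = 1052.6, rounded up to 1053 analysed; 1053 / 0.55 = 1914.5, rounded up to 1915 recruited. Both reproduce. Of the 1053 analysed, 1053 − 200 = 853 have no SBD.

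**2. Direction, with no assumed figures.** The FIT cut-off is 10 in both strategies, so

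referrals (OR rule) = referrals (FIT > 10) + number with FIT ≤ 10 and VOC > 0.63.

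The last term is zero or positive. Referrals cannot fall, and specificity cannot rise, relative to FIT alone.

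**3. Size among participants without SBD (illustrative).** Assumed: FIT specificity SpF 70–90%, VOC specificity SpV 50–80%, independence of the two tests. The documents give none of these.

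- Extra procedures versus FIT alone = 853 × SpF × (1 − SpV)
- Procedures avoided versus examining everyone = 853 × SpF × SpV

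| SpF | SpV | Extra versus FIT alone | Avoided versus examine-all |
|---|---|---|---|
| 0.7 | 0.8 | 119 | 478 |
| 0.7 | 0.5 | 299 | 299 |
| 0.9 | 0.5 | 384 | 384 |
| 0.9 | 0.8 | 154 | 614 |

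**4. All referrals, one example.** Dual sensitivity 97% (the design value); FIT sensitivity 80% (the article's figure for colorectal cancer at threshold 7, borrowed here for SBD at 10); both specificities 80%.

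- FIT alone: 0.80 × 200 + 0.20 × 853 = 331
- OR rule: 0.97 × 200 + (1 − 0.80 × 0.80) × 853 = 501
- Difference: about 170 more than FIT alone
- Against examining all 1053: about 552 fewer, made up of 0.64 × 853 = 546 without SBD and 0.03 × 200 = 6 missed SBD cases

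With FIT sensitivity from 53% to 86%, SpF from 70% to 90% and SpV among FIT-negatives from 50% to 100%, the addition ranges from (0.97 − 0.86) × 200 = 22 to (0.97 − 0.53) × 200 + 853 × 0.9 × 0.5 = 472.

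**5. Can the secondary scenarios reverse the direction?** The threshold grid runs upwards only, FIT from 10 to 120 and VOC from 0.63 to 1.

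- *AND rule.* It refers no more patients than FIT above 10, but its sensitivity cannot exceed that of FIT above 10. The Introduction puts FIT sensitivity at 80%, 53% and 86% for cancer, adenomas and inflammatory bowel disease at the lower threshold of 7. On those figures the required 97% is out of reach.
- *OR rule with raised thresholds.* It could refer fewer. With raised-threshold FIT specificity 97%, VOC specificity 95% and sensitivity still 97%, referrals are 0.97 × 200 + (1 − 0.97 × 0.95) × 853 = 261, against 331 for FIT alone. But raising thresholds can only lose sensitivity relative to the primary rule. From the article's single-test sensitivities and independence, the primary rule has 1 − 0.20 × 0.20 = 96.0% for cancer, 1 − 0.47 × 0.08 = 96.2% for adenomas and 1 − 0.14 × 0.14 = 98.0% for inflammatory bowel disease. There is little room to raise thresholds and hold 97%.

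**The case against.** Several points on the other side stand.

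- **A reduction can be counted elsewhere.** All participants enter because a clinician judged that they need colonoscopy or CTC, so an avoidable procedure in a patient without SBD naturally reads as a test-negative patient who was examined. That quantity is planned and can be estimated; what is missing is the named reference strategy.
- **FIT alone is a proper comparator.** The Introduction says that FIT triage is being introduced. Cost per QALY against FIT alone can validly show whether the extra procedures are worth the extra cases found, and this matches the stated objective of better detection.
- **The set-inclusion argument covers the base case only.** Raised thresholds or the AND rule could refer fewer patients, although they enter the model only as an optimistic sensitivity analysis and must meet the 97% requirement.
- **The FIT pathway in the model is not fully described.** The abstract's comparator might mean that FIT-negative patients are imaged later. The FIT strategy would then be close to examining everyone, and the sign could change. The Economic evaluation section, which speaks of selecting patients, points the other way. The model structure is only envisaged there, and pathway detail may sit in a fuller document that is not shown.

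A reader might infer that the study as a whole cannot show a reduction in colonoscopies, or that its economic evaluation is invalid. The documents support neither inference, for the first two reasons above.

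**Conclusion.** The point holds for the base-case economic comparison at the selection stage. There FIT plus VOC refers at least as many patients as FIT alone, so the contrast cannot show the reduction claimed in the abstract and Introduction. Under the primary rule that reduction can appear only against near-universal imaging, which the Introduction describes as current practice and the model does not name as a strategy.

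The direction rests only on the stated rule and on the same FIT cut-off of 10 in both strategies, with referral decided by the test result. The magnitudes (119 to 384 extra and 299 to 614 avoided among 853 participants without SBD) rest on assumed specificities and independence, and only illustrate how the sign depends on the comparator. The diagnostic accuracy analysis is unaffected. The gap limits what the economic evaluation can conclude about capacity and is worth closing before the model is built.

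**What to change.** 1. Add colonoscopy or CTC for all referred patients as a third modelled strategy, and run a fully incremental analysis of the three: examine all, FIT alone, FIT plus VOC. Keep the comparison with FIT alone.
2. Define avoidable procedures as those in test-negative patients without SBD, relative to examining everyone. Report beside this count the additional procedures under FIT plus VOC relative to FIT alone.
3. State in the Introduction which comparator the claim of fewer referrals refers to.
4. Reconcile the abstract's description of the comparator with that in Economic evaluation, and say what the model assumes about later imaging of FIT-negative patients.

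The cost is one more branch in a decision model that the article still describes as envisaged, plus a few sentences of text. No new data are needed: all participants are meant to undergo the reference examination, and its utility, resource-use and adverse-event inputs are already planned.
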